## Abstract

**Background:**

Studies have shown positive effects of therapeutic exercise on motor- and cognitive function as well as on psychosocial outcomes in persons with multiple sclerosis (MS). A reduction of inflammatory stress through physical exercise has been suspected as one key mechanism, mediating the positive effects of exercise in the context of MS. The primary objective of this trial is to investigate the acute and chronic effects of different exercise modalities on (anti-)inflammatory immune signalling as well as on cognitive and functional capacity in persons with MS.

**Methods:**

A two armed single-blind randomized controlled design will investigate 72 persons with relapsing remitting or secondary progressive MS (EDSS 3.0–6.0), during 3 weeks of inpatient rehabilitation. Participants will be randomized into either a high-intensity interval training (HIIT) or a moderate continuous training group; the latter represents the local standard therapy (ST). Both groups will exercise 3x per week. The HIIT group will perform 5 × 1.5-min high-intensive exercise bouts at 95–100% of their maximum heart rate (HR_max_) followed by active breaks of unloaded pedalling (60% HR_max_) for 2 min. In contrast, the ST group will exercise for 24 min continuously at 65% of HR_max_. The proportion of circulating regulatory T-cells will be measured as primary outcome. Secondary outcomes comprise numbers and proportions of further immune cells including Th17-cells, soluble factors ((anti-) inflammatory cytokines, tryptophan metabolites), endurance capacity, cognitive performance, processing skills for activities of daily living, fatigue, depression and healthcare-related quality of life. Outcomes will be assessed before (T_0_) and after (T_3_) the 3-week exercise intervention program. Blood samples of T_0_ will be taken immediately before the first exercise session. Additionally, blood samples for the soluble factors will be collected immediately after (T_1_) and three hours (T_2_) after the first exercise session of each group.

**Discussion:**

This study will be the first to investigate both acute and chronic effects of aerobic exercise on immune function and disease associated biomarkers in persons with MS. Combining biological analyses with cognitive and functional capacity assessments may contribute to a better understanding of responses to rehabilitative training, needed to improve exercise recommendations for persons with MS.

**Trial registration:**

This trial was prospectively registered at ClinicalTrials.gov (NCT03652519; 29 August 2018).

## Background

Several studies have shown positive effects of therapeutic exercise interventions on motor- and cognitive function as well as on psychosocial outcomes in persons with MS [1, 2]. Moreover, results from animal models and preliminary data in humans suggest that exercise could serve as a disease modifying supportive treatment [3–5]. Although the knowledge about the underlying biological mechanism provides hypotheses for improving training interventions and exercise recommendations for persons with MS, little controlled research has been conducted. As MS was shown to be accompanied or mediated by neuro-inflammation [6, 7], previously reported anti-inflammatory effects of physical exercise and training [8] have been hypothesized as a possible biological link contributing to the positive effects of exercise in persons with MS [9–11]. Furthermore, a chronic systemic inflammation is widely accepted as a common risk factor for many other chronic diseases (diabetes, cancer, Alzheimer’s disease, Parkinson’s disease, depressions) [12–14] and has further been observed in several patient populations suffering from fatigue and cognitive impairments [15]. It has been suggested that anti-inflammatory properties of exercise depend on two key mechanisms. First, regular exercise reduces visceral fat mass, a major source of inflammation, also known as “metflammation” (indirect effect) [16, 17]. Second, regular exercise and higher physical fitness levels are associated with increased numbers and proportions of circulating anti-inflammatory regulatory T-cells (T_regs_) (direct effect) [18]. T_regs_ suppress an over-activation of the immune system and produce anti-inflammatory cytokines (e.g. Interleukin (IL)-10 and Transforming Growth Factor beta (TGF-β)). The chronic increase in T_regs_ is interpreted as the body’s response to repetitive short-term inflammatory stimuli as they appear during and shortly after each bout of physical exercise, depending on exercise type, intensity and duration.

Interestingly, studies have shown that inflammatory stimuli, as they appear after acute exercise, activate the breakdown of the amino acid Tryptophan (TRP) within the Kynurenine (KYN) pathway [19]. In detail, inflammatory signals are known to induce the initial enzyme of this metabolic path (indoleamine 2,3-dioxygenase-1 (IDO1)) in various tissues, leading to a breakdown of TRP to KYN [20]. Moreover, acute exercise elevates circulating cortisol levels [21], a well described activator of the liver specific tryptophan 2,3-dioxygenase (TDO) [22], representing an isoenzyme of IDO1. KYN itself has previously been described to stimulate the differentiation of T_regs_ and to inhibit the activation of pro-inflammatory immune cells [23, 24]. Therefore, an acute exercise-induced activation of the KYN pathway may represent a possible explanation for chronic elevated numbers of T_regs_ together with further anti-inflammatory effects of exercise.

Besides the immune-modifying properties, chronic activation of the KYN pathway seems to play a pivotal and common role in the pathogenesis of several neurodegenerative disorders including MS [25, 26]. Elevated levels of KYN within the central nervous system lead to an accumulation of its neurotoxic metabolite quinolinic acid (QUIN) [27]. Recently, it was shown that physical exercise leads to a peripheral breakdown of KYN to kynurenic acid (KYNA) by inducing kynurenine aminotransferases (KATs) in muscle tissue [28]. In contrast to KYN, KYNA is unable to cross the blood brain barrier (BBB). Thus, physical exercise reduces the neurotoxic component of the KYN pathway, that was further described to be involved in cognitive dysfunction in neurological diseases [29, 30].

The described chronic anti-inflammatory effects of exercise may have further implications for MS. Recently we have shown that in contrast to moderate continuous training, intensive interval training chronically reduces serum levels of matrix metalloproteinase (MMP)-2 [9, 11]. MMP levels are upregulated by inflammatory stimuli and are further suspected to be involved in the pathogenesis of MS. More precisely MMPs increase the permeability of the BBB, leading to an alleviated infiltration of immune cells into the central nervous system [31].

In order to give more detailed recommendations for rehabilitative training programs it will be of major relevance to compare the influence of varying exercise modalities. Against this backdrop, the overall objective of the present study is to investigate acute and chronic effects of two different aerobic exercise programs on the immune function in persons with MS during rehabilitation. Acute effects are defined as alterations between immediately before, directly after and 3 h after the first exercise session. Chronic effects represent potential changes of resting levels over a 3-week training period. Additionally, the use of patient-oriented outcomes (e.g. cognitive performance, fatigue, depression) will provide new insights into potential associations with biological markers.

## Methods/design

A two-armed single-blind randomized controlled trial design will be adopted. Prior to inclusion, participants will be asked to provide written informed consent. Participants will be randomized into two different training groups performing either high-intensive interval (HIIT), or moderate continuous (ST) aerobic exercise training on a bicycle ergometer over a period of 3 weeks. Both groups will be assessed on the cardiopulmonary exercise test (CPET) before and after the intervention period. The training performed within both groups will be supervised by independent physiotherapists who will be blind to all other study assessments. The principal investigator will complete CPET and data analysis blinded to the training condition. Participants will not be blinded regarding their individual training intensity. The study design will contain four measurement time-points, considering both acute and chronic effects of each exercise training modality (see Fig. 1). All outcome parameters will be assessed at baseline within a period of 48 h before the first exercise session (T_0_) and at the end of the 3-week exercise training intervention, 48 h following the last training session (T_3_). Blood samples at baseline (T_0_) will be taken immediately before the first exercise session. Outcome changes between T_0_ and T_3_ will indicate the effects of chronic exercise training. Additionally, blood samples will be taken immediately after completion of the first exercise session (T_1_) and 3 h after completion of the first exercise session (T_2_) to provide further information on the acute effects of different exercise modalities on (anti-) inflammatory factors, TRP metabolites and BBB markers. The measurement time point T_2_ is implemented in the study design to examine the kinetics of soluble factors in response to a single-bout of exercise.

**Fig. 1 Fig1:**
[figure not shown]
Experimental design of the planned study. Baseline assessments will be conducted before the first training session (T_0_) and will be used as baseline value for both acute and chronic exercise training effects. Measurement time points T_1_ (immediately after first training session) and T_2_ (3 h after first training session) are implemented to examine the acute effects of each exercise modality on soluble factors. All assessments will be repeated 48 h after the last exercise session (T_3_) to investigate effects of chronic training following the 3-week exercise intervention

This study was approved by the regional ethics committee (EKOS) (EKOS18/96; Project ID: 2018–01378).

### Participants and randomization

Participants will be consecutively recruited on the day of admission for inpatient rehabilitation in the Valens Rehabilitation Center (Switzerland). They will be screened for study inclusion during a 12-month period. Key inclusion criterion for the participants’ eligibility will be a definite MS diagnosis (according to the revised McDonald criteria [32]) with relapsing remitting or secondary progressive MS phenotype and an Expanded Disability Status Scale (EDSS) [33] score between 3.0 and 6.0 (inclusive). Participants will be excluded if they experience acute severe relapses during the 3-week study, are given immune-modulating medication the day of CPET at baseline or T_3_, or withdraw their consent to participate. Detailed information for in- and exclusion criteria are shown in Table 1.

**Table 1 Tab1:** In- and exclusion criteria

INCLUSION	EXCLUSION
• *Relapsing remitting* or *secondary progressive MS*	• Pregnant or breast feeding women
• *EDSS: 3.0 – 6.0*	• Women planning to become pregnant during study period
• *Age > 21 years*	• Concomitant diseases (internistic, neurological or orthopaedic) limiting the execution of the intervention and assessments or affecting study endpoints
• Informed *consent* as documented by signature	• Drug or alcohol abuse
	• Problems of understanding (not German-speaking), psychological disorders, dementia etc. affecting the ability to understand study course and execute study instructions
	• Persons who already participated in the current study
	• Enrolment of persons employed for study execution, family members of the investigator and himself
	• Acute melanoma and cancer diseases under treatment of chemotherapy or radiation therapy

Participants will be randomly allocated (1:1) to one of the two training programs. Randomization will be conducted using “Randomization-In-Treatment-Arms” software (RITA, Evident, Germany). Randomization will follow the minimization procedure according to Pocock and Simon (for review see Scott et al. [34]) using disease severity (EDSS score), fatigue, age and level of cardiorespiratory fitness as factors for stratification.

### Study intervention

Treatment in both groups consists of specific endurance exercise modalities. Both groups will exercise 3 times per week over a period of 3 weeks on a bicycle ergometer. Exercise sessions will be supervised by physiotherapists. Exercise intensity will be regulated based on HR_max_ determined during the initial CPET. Exercise sessions in both groups will include a warm-up and a cool-down period at low intensity (50% HR_max_) for 3 min each.

#### Experimental intervention group (HIIT)

The experimental intervention group will receive a HIIT consisting of physiologically defined heart rate controlled cycling with 80–100 rpm (rpm) at 95–100% of HR_max_. The HIIT group will perform 5 × 1.5-min high-intensive exercise bouts at 95–100% of their HR_max_ followed by active breaks of unloaded pedalling over 2 min with the aim to achieve 60% of HR_max_.

#### Control group (ST)

In contrast, the ST group will exercise for 24 min continuously at 65% of participants’ HR_max_. (60–70 rpm). The ST group exercise modalities follow the standard therapy regime of the Valens clinic.

### Outcomes and assessments

#### Primary outcome

The primary outcome of this study is the change in proportions of circulating T_regs_ over the 3-week training period (T_0_ to T_3_). Blood samples will be taken by doctors or specialised nurses, via vein puncture from the antecubital vein in a seated position at T_0_ immediately before the first training session and at T_3_ after 3 weeks of training. Patients will be given 10 min between sampling and start of the exercise session to recover from any inconvenience caused by the vein puncture. All blood samples will be taken in K2 EDTA-tubes and Buffy-coat will be collected by centrifugation. Buffy-coat will be stored at − 150 °C until study completion. All samples will be analysed using flow cytometry to evaluate the proportions of T_regs_. T_regs_ will be assessed as CD3^+^CD4^+^CD25^+^ and CD127^dim^.

#### Secondary outcomes

All secondary outcomes will be assessed at baseline (T_0_) and after the 3-week training intervention (T_3_). To examine acute effects of the first exercise session blood samples will be additionally taken straight after completion of the first exercise session during cool down (T_1_) with the participant still seated on the ergometer as well as three hours after completion of the first exercise session (T_2_).

Blood samples for secondary outcomes at T_0_ and T_3_ will be taken at the same time as those of the primary outcome by using additional K2 EDTA- tubes for buffy-coat and plasma isolation. Plasma will be stored at − 80 °C until study completion. Moreover, cognitive and functional capacity data will be collected to identify potential associations with biomarker changes and to get better insight into the impact of different exercise training modalities. For a detailed overview of all outcomes and its assessments during the study period please see Fig. 2. The following will be captured as secondary outcomes:

**Fig. 2 Fig2:**
[figure not shown]
Spirit diagram depicting the schedule of enrolment, interventions and assessments. T_0_ = baseline assessment before the first exercise session; T_1_ = immediately after the first exercise session; T_2_ = three hours after the first exercise session; T_3_ = 48 h after the last exercise session. * Cardiorespiratory fitness and fatigue score are used as stratification factor and will be assessed before allocation

##### Immune status

An immune status including numbers and proportions of lymphocytes, T-cells (CD3^+^), NK-cells (CD3^−^CD56^+^) and B-cells (CD3^−^CD19^+^) will be assessed at T_0_ and T_3_. Furthermore, the T-cells subpopulations cytotoxic T-cells (CD3^+^CD8^+^), T-helper cells (CD3^+^CD4^+^), TH-17 cells (CD3^+^CD4^+^CD161^+^CCR6^+^), naïve T-cells (CD4^+^CD45RA^+^) as well as memory T-cells (CD4^+^CD45RO^+^) will be identified. Additionally, numbers of T_regs_ (CD3^+^CD4^+^CD25^+^ and CD127^dim^) will be assessed. Numbers and proportions will be determined by using flow cytometry. Gating strategies will be applied as reported by Zimmer et al. and Wenning et al. [35, 36].

##### Soluble factors

Inflammatory (Tumor necrosis factor-alpha, Interferon-gamma, IL-6, IL-17) and anti-inflammatory (IL-10, TGF-β) soluble factors as well as Tryptophan metabolites (TRP, KYN, KYNA, QUIN) that are known to be produced or secreted in response to exercise and that are further suspected to modify immune homeostasis and BBB function (MMP-2, MMP-9) through their inflammatory and anti-inflammatory properties will be measured at all time-points (T_0_ – T_3_). Therefore, plasma levels of TRP, KYN, TNF-alpha, IFN-gamma, IL-6, MMP-2, MMP-9, IL-10, TGF-beta and IL-17 will be determined using Enzyme-linked immuno-sorbent assay (ELISA) according to manufactures instructions. Levels of KYNA and QUIN will be assessed by high-performance liquid chromatography.

##### Cognitive performance

Cognitive performance will be assessed at T_0_ and T_3_ with the Brief International Cognitive Assessment for Multiple Sclerosis (BICAMS) [37] and a Go/No-Go test paradigm of the test battery of attention performance (*TAP*) [38]. The BICAMS is a battery involving three brief tests to assess the main cognitive domains vulnerable to MS: information processing speed, verbal and visual memory. The tests are the Symbol Digit Modalities Test (SDMT), the Verbal Learning and Memory Test (VLMT) and the Brief Visuospatial Memory Test revised (BVMT-R). Parallel versions of each test will be applied at T_3_.

The SDMT assesses information processing speed. Digits from one to nine are each paired with one of nine abstract symbols. The test consists of 110 of these nine symbols arranged in rows pseudo-randomly. The participant is instructed to name the corresponding number of each symbol, over 90 s after a training part of ten symbols is completed. The overall execution of the SDMT which includes the instructions, the training and testing parts takes 5 min.

The VLMT consists of a 15-item word list which is read aloud to the participant who is then asked to recall as many words as possible. The VLMT compromises 5 trials of which each includes a reading of the list and a repetition of the words by the participant. A defined order for repetition does not exist. The VLMT takes 5–10 min.

The BVMT-R compromises six abstract geometric figures located on a 2 × 3 array. The stimulus sheet is shown to the participant for 10s. After its removal the participant is asked to draw as many figures as possible from memory in the correct location, shape and proportion. There are three learning trials of 10s each after which the participant is required to draw the symbols. The drawing of the trial before is not visible for the participant during the other trials.

In addition to the BICAMS, the Test of attentional Performance (TAP), a classical Go/No-Go test paradigm will be completed [39]. Go/No Go paradigm tests are used to assess the ability to perform an appropriate reaction under time pressure and to simultaneously inhibit a formed behavioural response (automatic inhibition) [40]. In this paradigm, the focus of attention is directed to predictably occurring stimuli that require a selective reaction (to react if “x” appears and not to react if “+” appears, during 2 min). The TAP takes approximately 5 min.

##### Activities of daily living (ADL)

The performance of individuals’ activities of daily living will be evaluated using the AMPS. [41] This assessment will be conducted by experienced occupational therapists who participated in a training course for AMPS administration and were calibrated as reliable AMPS raters. Four individual activities of daily living, which the participant is familiar with, will be identified in accordance with the AMPS assessor. Therefore, the participant will select the tasks from the AMPS manual including standardized activities of daily living. The selected tasks must be part of the participant’s everyday life. Two of the chosen four tasks will be performed in the assessment. For the evaluation of individual’s performance, 16 motor and 20 process skill items will each be evaluated by the AMPS rater on a 4-point scale. 4 points are defined as a performance which is conducted effortlessly and safely whereas 1 point is given for performances which for example hold serious deficits concerning safety and efficiency [41]. Higher positive scores are indicative of higher ability. AMPS will be performed at T_0_ and repeated after the training intervention at T_3_.

##### Cardiorespiratory fitness

Cardiorespiratory fitness will be assessed through a progressive CPET performed at baseline on a cycle ergometer (Ergoline 800, Germany) immediately before group allocation because results will be used as stratification factor. CPET will be repeated at T_3_ 48 h after the last exercise session. Details on the protocol can be found elsewhere [42]. The individual cardiorespiratory fitness level is monitored by direct and continuous measurements (breath by breath) of peak oxygen consumption (VO2_peak_) by ergospirometry (PanGas CPX, Germany).

VO2_peak_ is defined as the highest VO2 value when the following criteria are attained: respiratory equivalent ratio > 1.10; peak heart rate within 10 min-1 of age predicted maximum and rating of physical exertion (RPE) > 8.5 as reported by Wassermann et al. [43].

##### Fatigue

Fatigue will be assessed with the multidimensional FSMC scale [44] before CPET under resting conditions. FSMC has defined cut-off scores to classify mildly, moderately and severely fatigued patients. Cut-off for fatigue for the total score is set at 43 and at 22 for the motoric and cognitive sub-scores. The scale has good test-retest reliability and has been translated into German. The fatigue score will be used as a stratification factor, hence, it will be assessed before allocation and repeated at T_3_.

##### Depression and anxiety

Depression and anxiety will be assessed at T_0_ and repeated at T_3_ with the Hospital Anxiety and Depression Scale (HADS) for adults with physical ailments [45]. The questionnaire consists of 14 items, 7 for anxiety and 7 for depression, with higher scores indicating more severe anxiety or depression.

##### Healthcare-related quality of life

Healthcare-related quality of life will be assessed using the Patient-Reported Outcome Measurement Information System (PROMIS) short form Global-10 [46] at T_0_ and will be repeated at T_3_. The PROMIS Global-10 consists of 10 items that separately measure different aspects of perceived symptoms and functioning.

### Safety

Tolerability (safety) of the 3-week training program, and of each bout of exercise for persons with MS, will be monitored by continuous heart-rate measurements. Heart rate (beats per minute) during and after the exercise sessions in both intervention groups should not exceed 220 minus age. This prevents worsening of sensory symptoms and allows normalization within half an hour after the exercise sessions. Moreover, the dropout-rate will be captured in total and for each group.

All severe adverse events - that include i) severe cardiovascular and pulmonary diseases (renal failure, hepatic dysfunction, cardiovascular disease) and ii) severe cardiovascular exacerbations (e.g. RR > 240/120, HR above the age predicted maximum of 220-Age) during training – will be directly reported to the ethical committee.

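### The HIIT target is tied to measured maximum heart rate but the safety limit to 220 minus age, so correctly delivered HIIT can count as a reportable severe adverse event

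*Protocol article*

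**What the plan says.** Under Study intervention, the protocol article ties training load in both arms to a measured value: "Exercise intensity will be regulated based on HR_max_ determined during the initial CPET". The HIIT section then prescribes "5 × 1.5-min high-intensive exercise bouts at 95–100% of their HR_max", and the control section has participants "exercise for 24 min continuously at 65% of participants" of the same measured quantity.

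The Safety section works from an age formula instead: "Heart rate (beats per minute) during and after the exercise sessions in both intervention groups should not exceed 220 minus age". In the list of severe adverse events to be reported directly to the ethics committee, the same section gives as examples "severe cardiovascular exacerbations (e.g. RR > 240/120, HR above the age predicted maximum of 220-Age) during training".

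No section limits the HIIT target to 220 minus age, and none says which rule governs when the two disagree.

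**The concern.** A measured maximum heart rate and 220 minus age are different quantities for the same person. Where the measured value is the higher of the two, a physiotherapist who delivers the top of the HIIT band exactly as written takes the participant over the limit. The session is correctly delivered and is also a reportable severe event.

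Two things are at stake. Supervising staff have instructions that diverge for some participants. And the event criterion is not neutral between arms: it can be met by following the prescription in HIIT but not in standard therapy, so counts of severe events by arm would partly reflect the definition and not tolerability.

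**Working it through.** The plan states no figure on this point, so there is nothing to reproduce. The check is arithmetic on its own rules.

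**Inputs from the protocol article**
- HIIT band: 95–100% of measured maximum heart rate, M (Study intervention; HIIT section).
- Control target: 65% of M (Control group section).
- Limit: L = 220 − age (Safety).
- HIIT arm: 72 recruited, allocated 1:1, so 72 / 2 = 36.

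**When the band crosses the limit.** Write M = L + d, where d is measured minus predicted.
- The top of the band is L + d. It is above L whenever d > 0.
- The bottom is 0.95(L + d). It is above L when d > L/0.95 − L = L/19.
- If d ≤ 0, no part of the band is above L.

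| Age | L | d above which the whole band exceeds L | Band at d = 5 | Band at d = 10 |
|---|---|---|---|---|
| 30 | 190 | 10.0 | 185.25–195 | 190–200 |
| 40 | 180 | 9.5 | 175.75–185 | 180.5–190 |
| 45 | 175 | 9.2 | 171–180 | 175.75–185 |
| 50 | 170 | 8.9 | 166.25–175 | 171–180 |
| 60 | 160 | 8.4 | 156.75–165 | 161.5–170 |

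At age 45 with d = 5, the band is 9 beats wide and 5 of them lie above 175 (5/9 = 56%); 171–175 satisfies both rules. With d = 10, 0.95 × 185 = 175.75 > 175, so no heart rate satisfies both.

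**Control arm.** Reaching L at 65% of M needs M = L/0.65. At age 50 that is 170/0.65 ≈ 262, which is not realistic.

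**How many are affected.** The documents do not say. *Assumption:* d is normal with SD 10 and mean μ. Some overlap has probability P(d > 0) = 1 − Φ(−μ/10). Full incompatibility, using the age-45 threshold for everyone, has probability P(d > 9.2) = 1 − Φ((9.2 − μ)/10).

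| μ | Some overlap | Of 36 | Full incompatibility | Of 36 |
|---|---|---|---|---|
| 0 | 50% | 18.0 | 18% | 6.4 |
| −5 | 31% | 11.1 | 8% | 2.8 |
| −10 | 16% | 5.7 | 3% | 1.0 |
| −20 | 2% | 0.8 | 0.2% | 0.1 |

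Each affected participant has 3 × 3 = 9 sessions of 5 bouts, so 45 bouts in which the limit could be crossed.

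**The case against.** A training target with a separate safety limit is not in itself a contradiction, and the limit is worded as something that should not be exceeded, not as a prohibition. Staff could treat it as an implicit cap. This part fails. The article does not state a cap, the same crossing is named as a severe adverse event, and once the excess passes about 8–10 beats a cap would remove the entire prescribed band. Nor is this a detail left to a fuller document: both rules are stated, and they disagree.

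Other parts of the objection stand, and they rule out several stronger readings.

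- *Both rules can never be followed once the measured maximum exceeds 220 minus age.* Not so: with a small excess the lower part of the band complies.
- *Up to 18 of 36 participants face an impossible instruction.* That count is for any overlap, under assumed values. The corresponding count for full incompatibility is about 6.
- *The exercise test's own criteria approve a training maximum above prediction.* The condition "peak heart rate within 10 min-1 of age predicted maximum" belongs to the definition of peak oxygen consumption. It does not regulate the heart rate used to set training. The supportable statement is that no section rules out a higher value.
- *The contrast between arms is lost.* At age 45 with a measured maximum of 185, holding at the limit gives 175/185 = 94.6%, against 65% in the control arm.
- *The safety comparison becomes uninterpretable.* The article plans capture by group only for dropout and describes no formal safety comparison, so this goes too far.

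**Conclusion.** The inconsistency is real but conditional. It concerns HIIT participants whose measured maximum exceeds 220 minus age. For them, correctly delivered training can trigger a report of a severe adverse event, and strict incompatibility needs an excess of roughly 8–10 beats. This follows from the protocol's own rules and needs no outside figure.

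The frequency does rest on an assumption. With SD 10 and mean difference 0 to −20, some overlap affects about 18 to 1 of 36 and full incompatibility about 6 to 0. A different mean or SD would change these counts.

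Because the control target lies far below the limit, such events would fall almost only in the HIIT arm and would distort any reading of tolerability by arm. No effect on the primary regulatory T-cell outcome is shown.

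**What to change.** Before the first HIIT session, reconcile the Study intervention, HIIT and Safety sections so that the training target, the heart-rate limit and the severe-event definition are consistent with one another. Which rule applies is for the clinical team to decide; this review takes no position on it. In the safety reporting, show crossings of the heart-rate limit separately from other severe adverse events, by arm, so that events arising from the definition can be told apart from the rest.

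The cost is a protocol clarification and one extra reporting line. Design, sample size and primary analysis are unaffected.
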